**Figure 3 fig3:**
[figure not shown]
Location of acupoints and sham acupoints.

##### Acupoint location

The acupoint locations were referenced from the 2010 WHO standard (ISBN: [contact]). The acupoint locations are shown in Table 1 and Figure 3.

##### Material preparation

Needles: Huatuo brand disposable sterile acupuncture needles, produced by Suzhou Medical Supplies Factory Co., Ltd., with specifications of Φ0.30 mm × 40 mm, will be used.

Other Materials: 75% alcohol for disinfection and sterile dry cotton swabs will be used.

##### Operation method

The acupuncture treatment will follow a standardized procedure. The operator will disinfect their hands. The patient will first sit up, and the Fengchi point (GB 20) will be disinfected. The operator will then insert the needle at a depth of 0.8–1.2 cun, angled toward the tip of the nose at Fengchi (GB20), and will withdraw it after achieving Deqi (a sensation that may include soreness, numbness, distention, or heaviness). The patient will then lie supine, and the acupoints Baihui (GV20), Sishencong (EX-HN1), Benshen (GB13), and Shenting (GV24) will be disinfected and needled at a depth of 0.5–0.8 cun. Yintang (GV24+) will be needled downward at a depth of 0.5–1 cun; Shuigu (GB8) at a depth of 0.5–0.8 cun; and Neiguan (PC6) and Taichong (LR3) at a depth of 0.5–0.8 cun. All needling points will be required to achieve Deqi, and after achieving Deqi, the needles will be retained for 30 min.

A “cun” is a proportional body measurement unit used in acupuncture, defined relative to each patient’s anatomical landmarks. For example, the distance between the two ends of the skin crease of the interphalangeal joint of the patient’s middle finger, when flexed, is considered 1 cun. Deqi (obtaining qi) refers to a composite of needle sensations, including soreness, numbness, heaviness, and distension, which indicate effective acupuncture stimulation and are considered important for the therapeutic response. In this trial, deqi will be assessed by practitioners through tactile feedback (needle grasp and tissue response) and patient-reported sensations after gentle needle manipulation.

##### Treatment course

The treatment will be administered every other day, three times per week, for a total of 6 weeks. During the treatment course, symptom assessment and clinical safety evaluation will be conducted as needed, monitoring for adverse events, recording concomitant medications, and documenting protocol deviations. Case report forms (CRFs) will be completed.

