### Blinding

Due to the specific nature of acupuncture, it is not feasible to blind practitioners. Therefore, blinding will be implemented for the participants, evaluators, and statisticians. Practitioners adhere to strict confidentiality protocols to avoid disclosing group allocation to the participants and evaluators. Evaluators are responsible for collecting and analyzing the data unrelated to the treatment process and are not exposed to any information about group allocation throughout the study. Statisticians are solely responsible for data analysis and are not involved in the treatment process, thereby ensuring the objectivity and impartiality of the results.

To evaluate participant blinding integrity, Bang’s Blinding Index (BI) will be calculated at the completion of the treatment phase (17). After the final treatment session, the participants will be asked to guess their group allocation (real acupuncture, sham acupuncture, or unsure) and to rate their confidence in this guess.

The Credibility/Expectancy Questionnaire (CEQ) (18) will be administered after the first treatment session. Group differences in the CEQ scores will be examined to verify that expectancy was balanced between the groups.

After the completion of statistical analysis, the unblinding procedure will be initiated. Researchers responsible for unblinding will disclose group information to the data analysts as necessary to finalize comparisons and interpret the study results.

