#### Concomitant treatment and follow-up

During the 8-week follow-up period, symptom assessment and clinical safety evaluation will be performed, with monitoring for adverse events, recording protocol deviations, and completing CRFs. During the study, no additional medications will be used by the participants. If pain due to migraine necessitates the use of painkillers, each instance of medication use must be reported to the researcher, with detailed records of the medication name, specifications, dosage, time of use, and symptom relief documented.

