### Safety monitoring and adverse event reporting

To maximize participant safety and proactively minimize risks, all participants will undergo a careful anamnesis and baseline assessment before the first treatment. During the study, the participants undergoing acupuncture treatment may experience adverse events (AEs), including but not limited to pain, subcutaneous congestion, hematoma, local infection, and, in rare cases, severe events such as syncope. Safety assessments will encompass vital sign measurements (blood pressure, heart rate, respiration rate, body temperature) and physical examinations. These vital sign measurements will be performed before the start of the protocol (at baseline assessment) and at key points during the treatment period (before and after treatment). Their primary purpose will be to monitor participant safety and ensure early detection of potential adverse reactions, rather than to serve as clinical indicators of acupuncture efficacy. Detailed documentation of AEs will include the time of occurrence, duration, classification, severity, remedial actions, and final resolution. Participants will be instructed to report any abnormal reactions or discomfort, which will be carefully documented, including the time, severity, and potential causes. Regardless of their relationship to the treatment, all AEs will be promptly and appropriately managed, recorded in the Case Report Forms (CRFs), and reported to the study director and the Ethics Committee of the Affiliated Hospital of Shandong University of Traditional Chinese Medicine.

Mild and moderate AEs will be managed symptomatically and monitored, while severe AEs, such as death, life-threatening disability, or hospitalization, will receive emergency treatment and will be reported to the Research Ethics Committee within 24 h, which will provide guidance on whether the trial should be terminated. To minimize the risk of severe adverse events, all practitioners have received specific training on recognizing and managing autonomic adverse responses to acupuncture, consistent with safety guidelines outlined in recent systematic reviews (29, 30).

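### Safety evaluation during the needling weeks has no fixed schedule, fits poorly with the article's own safety section, and leaves the between-arm adverse event comparison open to differential ascertainment

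*Protocol article*

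**What the plan says.** - **Treatment course** (three sessions a week for six weeks): "symptom assessment and clinical safety evaluation will be conducted as needed, monitoring for adverse events". No session or interval is fixed. The Control group section gives the sham arm the same course, so this wording governs both arms.
- **Concomitant treatment and follow-up** (eight weeks without needling): "During the 8-week follow-up period, symptom assessment and clinical safety evaluation will be performed, with monitoring for adverse events". The discretionary qualifier is absent.
- **Safety monitoring and adverse event reporting**: "Safety assessments will encompass vital sign measurements (blood pressure, heart rate, respiration rate, body temperature) and physical examinations". Vital signs are taken at baseline and "at key points during the treatment period (before and after treatment"). The points are not defined, and physical examinations are given no times.
- The same section adds two safeguards: "Participants will be instructed to report any abnormal reactions or discomfort, which will be carefully documented", and "Regardless of their relationship to the treatment, all AEs will be promptly and appropriately managed, recorded in the Case Report Forms (CRFs") and reported.
- **Blinding**: participants, evaluators and statisticians are blinded and practitioners are not. On the evaluators' task: "Evaluators are responsible for collecting and analyzing the data unrelated to the treatment process". AEs are not mentioned there.
- **Data management**: the investigator completes the case report form; whether that person is blinded is not stated.
- **Data analysis**: treatment-related AEs are compared between the arms by a chi-squared or Fisher's exact test, at 0.05.

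**The concern.** The harms that the article lists (pain, subcutaneous congestion, hematoma, local infection, syncope) are mainly complications of needling. The discretionary wording thus applies to the weeks of exposure, and the firmer wording to the weeks without needling. Someone has to judge when an evaluation is needed. The practitioner is the one person certain to be at every session, and knows whether the needle went in 0.5 to 1.2 cun with Deqi or about 2 mm without manipulation. If the intensity of looking follows that knowledge, in either direction, part of any observed difference in AE incidence is a difference in looking.

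This matters because the AE comparison is a planned between-arm test, and a low AE incidence is part of the case that the Introduction makes for acupuncture. Comparing all AEs in place of treatment-related ones would not remove the problem, because it concerns how events are found, before anyone judges relatedness.

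**Working it through.** **Step 1. The stated rules side by side.**

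| Period | Section | Rule for safety evaluation | Times fixed? |
|---|---|---|---|
| Weeks 1–6, 3 × 6 = 18 sessions | Treatment course | when needed | no |
| Weeks 1–6 | Safety monitoring | vital signs before and after treatment, at unnamed points | partly |
| Weeks 7–14 | Concomitant treatment and follow-up | performed, no qualifier | no, but not discretionary |

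A planned before-and-after measurement and an evaluation done only when needed are different rules for the same weeks. A site could follow either one and claim compliance.

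**Step 2. How an AE can reach the case report form.**

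- Spontaneous report by a blinded participant: stated.
- Recording of every AE whatever its cause: stated, but this covers only events that have already come to light.
- Vital signs: stated. They may catch syncope; they are not a means of finding a hematoma or a local infection.
- Physical examination: stated, without times.
- Scheduled question put to every participant: not stated.
- Blinded person named to elicit AEs: not stated.

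**Step 3. What unequal capture would do.** The article gives no AE incidence and no capture rate, so there is no figure of the plan to reproduce. Everything below is assumed.

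Inputs from the article: n = 120 and 60; chi-squared test at two-sided 0.05. Assumed: true incidence p, equal in both arms, and capture rates c₁ (acupuncture) and c₂ (sham). Observed incidence in arm i is p × cᵢ. The rejection probability is the sum of Bin(x; 120, p·c₁) × Bin(y; 60, p·c₂) over all (x, y) at which the uncorrected chi-squared test rejects.

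| p | c₁ | c₂ | Observed | Ratio | Rejection probability |
|---|---|---|---|---|---|
| 20% | 100% | 100% | 20% vs 20% | 1.00 | 5.1% |
| 20% | 90% | 80% | 18% vs 16% | 1.13 | 5.9% |
| 20% | 80% | 90% | 16% vs 18% | 0.89 | 6.6% |
| 20% | 90% | 60% | 18% vs 12% | 1.50 | 16.8% |
| 20% | 60% | 90% | 12% vs 18% | 0.67 | 20.4% |
| 10% | 100% | 60% | 10% vs 6% | 1.67 | 12.7% |
| 30% | 100% | 60% | 30% vs 18% | 1.67 | 41.5% |

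A ten-point gap in capture leaves the test close to its nominal level. A gap of 30 to 40 points does not. Nothing in the document says which row applies, or that capture is unequal at all. The example treats AEs of all kinds alike, whereas the planned test is on treatment-related AEs.

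**The case against.** The case on the other side has real weight.

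- **A reader might infer that safety is looked at only when someone thinks it necessary.** The document does not support that. Its dedicated safety section plans vital signs, includes physical examinations, instructs participants to report any discomfort, and requires every AE to be recorded. Those participants are blinded and attend three times a week, so they have frequent chances to report.
- **A reader might infer that unblinded practitioners decide when AEs are sought.** No section says so, and none names who decides. The practitioner is the likely person, but that is an inference.
- **A reader might infer that blinded evaluators are barred from AE data.** The Blinding section does not mention AEs. Its wording can simply mean that evaluators take no part in treatment, as the parallel sentence on statisticians says.
- **A reader might infer that AE rates in the two arms cannot be compared.** Both arms have the same course and the same safety text, and no differential procedure is stated.
- **This is a journal article.** Named sessions, checklists and the person who asks about AEs may stand in the full protocol or case report form, and their absence here is no error in itself.

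All five stand, and they limit the point. They do not remove it. The discretionary wording is in the article's own text and does not agree with its own safety section. Spontaneous reporting and a rule to record all AEs do not amount to a uniform enquiry. The same discretion in both arms does not ensure the same use of it where its likely user knows the arm.

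**Conclusion.** The point holds in a limited form. The Treatment course and Safety monitoring sections give rules for the needling period that do not fit together and must be reconciled. As written, the article relies on evaluation when needed plus spontaneous reporting, states no scheduled elicitation, and names no blinded role for it. The between-arm AE comparison is therefore open to differential ascertainment.

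That bias is possible, not shown, and its size cannot be derived from the document. Under the assumed rates above, the false-positive rate of the AE test runs from about 6% with a small gap in capture to 17% to 20% with capture of 90% against 60% at 20% incidence; it would be higher with more frequent AEs and a wider gap. The AE comparison is neither the primary nor a listed secondary outcome, and the efficacy analysis is untouched. This is an inexpensive improvement, not a flaw that threatens the trial.

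**What to change.** 1. Reconcile the Treatment course and Safety monitoring sections. Replace the discretionary wording in the first and the unnamed key points in the second with one set of named assessment times, identical in both arms. Which times these are is for the investigators to decide.
2. Add one scripted, open AE question covering the interval since the last contact, asked of every participant at each of the 18 existing sessions and at the week 10 and week 14 assessments that the secondary outcomes already use. Record it on a participant-completed form, or through an existing blinded evaluator where one is present.
3. If the full protocol or case report form already fixes these times and the person who asks, a sentence in the article saying so is enough.

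**Cost.** Changes to protocol and case report form wording, and a minute or two per session; no extra visits, and no extra staff with a participant-completed form. Recorded AE counts will rise in both arms. Recruitment is scheduled to the end of 2026, so the change can reach only participants still to be treated or followed. The report should give the date of the change, and the AE comparison should be shown separately before and after it.

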#### Control group

The sham acupoint locations that will be employed in this trial have been selected based on validated protocols from previous migraine acupuncture RCTs (25–27). These non-acupoint positions meet three critical design criteria: (1) anatomical validity—located outside traditional meridian pathways to minimize point-specific activation; (2) sensory similarity—positioned to provide comparable tactile sensations for maintaining participant blinding; and (3) established precedent—these sham points have been validated across multiple high-quality migraine trials, including large-scale studies demonstrating successful group differentiation. The control group will receive sham acupuncture at the designated Sham acupoints.

All Sham acupoints will be shallowly needled bilaterally at a depth of approximately 2 mm. No needling manipulation will be performed, no qi will be obtained, and needles will be retained for 30 min. Needle specifications and the treatment course will be the same as those in the treatment group (Table 1 and Figure 3).

#### Concomitant treatment and follow-up

During the 8-week follow-up period, symptom assessment and clinical safety evaluation will be performed, with monitoring for adverse events, recording protocol deviations, and completing CRFs. During the study, no additional medications will be used by the participants. If pain due to migraine necessitates the use of painkillers, each instance of medication use must be reported to the researcher, with detailed records of the medication name, specifications, dosage, time of use, and symptom relief documented.

### Outcome measures

#### Primary outcome measures

The primary outcome measure is the change from baseline in the average number of monthly headache days during weeks 3–6 of the 6-week treatment period.

According to the headache diary, patients will be asked about the duration of headache, defined as the number of days on which the headache lasted for at least 4 h. Headaches will be considered according to the ICHD-III criteria: criteria C and D (1.1) for migraine without aura, criteria B and C (1.2) for migraine with aura, or criteria 1.6 for possible migraines. Patients will also be required to record, on days with a migraine or headache, successful treatment with trastum, ergot, or other migraine-specific acute drugs.

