## Introduction

Migraine is a neurovascular disorder that affects approximately 15.2% of the global population. It ranks as the second leading cause of health loss in terms of years lived with disability worldwide and is the leading cause among women aged 15–49 years (1). Chronic migraine (CM), defined by the International Classification of Headache Disorders, 3rd edition (ICHD-3), as experiencing headaches occurring on ≥15 days per month for >3 months with at least 8 days per month fulfilling criteria for migraine, represents the most severe form of migraine and affects approximately 1–3% of the general population (2). Compared to those with episodic migraine, patients with chronic migraine have a higher prevalence of depression and anxiety, dyspepsia, irritable bowel syndrome, epilepsy, chronic sinusitis, and many other disorders (3). Current pharmacological treatments for CM include oral medications such as topiramate, valproate, propranolol, and injectable botulinum toxin A (BoNT-A), as well as recently developed monoclonal antibodies targeting the calcitonin gene-related peptide (CGRP) pathway (4, 5). However, these pharmacological treatments may cause adverse events (AEs) such as hypotension, depression, somnolence, and gastrointestinal intolerance (6). These comorbidities and adverse events not only impose a greater burden on patients but also significantly impair their health-related quality of life, negatively affecting treatment response, medication adherence, and overall wellbeing (7). Therefore, the effective management of chronic migraine requires a comprehensive strategy that not only focuses on ameliorating headache symptoms but also prioritizes improving medication adherence, emphasizing daily disease management, and ultimately enhancing the patient’s overall quality of life.

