Acupuncture, a non-pharmacological therapy with a long history in Traditional Chinese Medicine, is increasingly recognized globally for its favorable safety profile and low incidence of adverse events (8, 9). Multiple high-quality systematic reviews (10, 11) and randomized controlled trials (RCTs) (12, 13) have consistently established the effectiveness of acupuncture as a prophylactic treatment for migraine, demonstrating significant long-term reductions in headache frequency and severity in the general migraine population. However, the majority of existing high-quality clinical studies have primarily focused on patients with episodic migraine, while dedicated research targeting patients with chronic migraine (CM), who experience more severe symptoms and greater management complexity, remains relatively limited (14). CM patients experience a significantly higher disease burden compared to EM patients (15), and the effective management of CM should adopt a comprehensive strategy that not only alleviates pain symptoms but also prioritizes improving medication adherence, managing the associated emotional burden, and ultimately enhancing the patient’s overall health-related quality of life (16).

Therefore, the present study is designed to rigorously evaluate acupuncture as a prophylactic treatment for chronic migraine using a multicenter randomized controlled trial. It is hypothesized that patients who receive acupuncture will demonstrate significantly greater reductions in monthly headache days, improved migraine-specific quality of life, and reduced acute medication use compared to those who receive sham acupuncture.

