### Sample size

The sample size was calculated using the PASS 11.0 software. Based on published literature (12), the number of migraine attack days was estimated as the outcome indicator for long-term efficacy observation. The number of migraine attack days in the acupuncture treatment group was reduced by 3.9 ± 3.0 days, while the number of migraine attack days in the sham acupuncture control group was reduced by 2.2 ± 3.2 days. The level of statistical significance was set at *α* = 0.05, and test efficacy was defined as (1-*β*) = 0.90. The ratio of the sample size between the treatment and control groups was set at 2:1, resulting in an estimated requirement of 107 participants in the treatment group and 54 in the control group. Considering potential dropout during the trial, with a predicted shedding rate of 10%, the initial number of participants was set at 120 in the treatment group and 60 in the control group, totaling 180 participants.

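### The primary outcome is named monthly headache days, but its only day count uses a 4 h threshold and migraine criteria, and no rule says whether headaches stopped early by acute drugs count

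*Protocol article*

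**What the plan says.** Under Primary outcome measures, the protocol article sets the outcome as the "change from baseline in the average number of monthly headache days during weeks 3–6 of the 6-week treatment period". The Abstract and Secondary outcome measures use the same name. Three sentences then bear on how a day is counted:

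- **Duration.** Patients are asked, from the diary, about headache duration, "defined as the number of days on which the headache lasted for at least 4 h".
- **Diagnosis.** "Headaches will be considered according to the ICHD-III criteria: criteria C and D (1.1) for migraine without aura"; corresponding criteria follow for migraine with aura and for possible migraine.
- **Acute treatment.** "Patients will also be required to record, on days with a migraine or headache, successful treatment with trastum, ergot" or another migraine-specific acute drug.

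Other sections add the following:

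- **Introduction, disease definition.** Chronic migraine requires headache on 15 or more days per month, "with at least 8 days per month fulfilling criteria for migraine".
- **Introduction, hypothesis.** Patients given acupuncture are expected to show "reduced acute medication use compared to those who receive sham acupuncture".
- **Concomitant treatment and follow-up.** Painkillers are allowed when migraine pain requires them. Each use is reported with its time and the relief obtained.
- **Secondary outcome measures.** Acute medication days are a separate outcome and are not part of the primary count.
- **Sample size.** The planning figures are for another label: "The number of migraine attack days in the acupuncture treatment group was reduced by 3.9 ± 3.0 days", against 2.2 ± 3.2 days with sham.

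**The concern.** There are two linked problems.

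First, three labels are used for what should be one count: headache days in the outcome's name, days with headache of at least 4 h judged by migraine criteria in its description, and migraine attack days in the sample size. Two competent analysts could derive different primary results from the same diaries. If the choice were made after unblinding, it could be made with the results in view.

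Second, a 4 h threshold with no rule for treated headaches makes the count sensitive to acute medication. A headache that would have lasted all day but is stopped by a drug within 4 h drops out on a literal reading. Acute medication use is itself an outcome that the trial expects acupuncture to lower. The primary count would then depend on something that the treatment is expected to change after randomisation.

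**Working it through.** **1. The plan's own figure.** Inputs from Sample size: reductions of 3.9 (SD 3.0) and 2.2 (SD 3.2), alpha 0.05, power 0.90, ratio 2:1, dropout 10%. The article does not say whether the test is one- or two-sided; the two-sided calculation is the one that matches.

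- Difference: 3.9 − 2.2 = 1.7 days.
- Control n = (3.2² + 3.0²/2) × ((1.960 + 1.282)/1.7)² = 14.74 × 3.636 = 53.6, so 54.
- Treatment n = 2 × 53.59 = 107.2, against 107 stated.
- With dropout: 107/0.9 = 118.9 and 54/0.9 = 60, against 120 and 60 stated.

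The sample size reproduces, so this point rests on no arithmetic error. What matters is that the 1.7 days is a difference in migraine attack days, while the outcome carries the name of headache days.

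**2. Do the labels describe different counts?** By the Introduction's definition, a patient at the entry minimum has 15 headache days, of which 8 meet migraine criteria. The gap is 15 − 8 = 7 days per month. This is a gap in levels at the threshold, not in change from baseline, and the primary outcome also admits possible migraine, which narrows it. It shows that the labels are not interchangeable; it does not estimate an effect on the result.

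**3. What happens to drug-shortened headaches?** For each patient and window, let

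- T = days with headache of at least 4 h, or with headache of any duration treated with acute medication;
- U = days in T on which the headache was treated and lasted under 4 h;
- L = T − U, the literal 4 h count.

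The same identity holds for reductions from baseline. Write D for the acupuncture reduction minus the sham reduction. Then

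D(L) = D(T) − D(U).

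If acupuncture lowers the number of drug-shortened days more than sham does, D(U) is positive and the literal count shows a smaller difference than T. Measuring change from baseline does not remove this, because D(U) arises after randomisation.

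**4. How firm is the direction?** The stated hypothesis concerns acute medication use overall, not the treated days under 4 h alone. D(U) above zero is therefore probable rather than certain.

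**5. How large is it?** The documents give no number of drug-shortened days, no acute medication days by arm, and no frequency of headaches ending before 4 h. D(U) cannot be calculated from them.

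**6. Which drugs are covered?** The recording sentence in the primary outcome names migraine-specific acute drugs only, whereas the concomitant-treatment section covers painkillers generally. A headache stopped by an ordinary painkiller is outside even the primary outcome's recording instruction, although the medication record should hold it.

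**The case against.** The strongest reply is that the text excludes nothing. The 4 h phrase is attached grammatically to the duration of headache, not to headache days. The ICHD sentence says how headaches are to be considered and does not expressly make the criteria a filter. The sentence on successful treatment stands within the primary outcome's description and may have been meant as a further way for a day to qualify. The article condenses a fuller protocol, which may hold the diary instructions. This stands in part: a reader might infer that the plan deliberately discards treated days, and the documents do not support that. It does not remove the problem, because the article offers no other operational count, and taken as written it leaves these days out.

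A reader might also infer a definite loss of power by subtracting some number of uncounted days from the 1.7-day difference. The documents do not support this either. They give no such number, and the 1.7 days comes from a cited study whose counting rule is not shown. If that study counted in the same way, its difference already includes the effect, and subtracting again would count it twice.

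Finally, a reader might conclude that the migraine criteria should be dropped from the primary count. That would suit the outcome's name but move it further from the migraine attack days used for the sample size. Either choice can be made coherent. It is also fair to say that a bias towards zero does not threaten a false claim of benefit; the risks are a missed or understated effect and an unclear estimand.

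**Conclusion.** The concern holds as a defect in the definition of the primary outcome. The article uses three labels for one count, and its own disease definition shows that headache days and migraine days differ. It gives no rule for headaches stopped by an acute drug before 4 h. On the literal reading these do not count, the primary count depends on acute drug use, and the arm difference is probably biased towards zero.

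The direction rests on two assumptions: that acute use is lower with acupuncture, as hypothesised, and that drug-shortened days fall along with it. The size of the bias cannot be quantified from the documents. The 7-day gap at the entry minimum shows how far the counts can differ in level and says nothing about the bias. The stated sample size is arithmetically sound for the label and difference it uses.

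**What to change.** Before unblinding, amend the protocol wording as follows:

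1. **One label.** Choose headache day or migraine day, and use it in the Abstract, Primary outcome measures, Secondary outcome measures and Sample size.
2. **One counting rule.** Apply it identically at baseline, in weeks 3–6 and in both follow-up windows. A day counts if the headache lasted at least 4 h, or if a headache of any duration was treated with acute medication. State that this covers any acute medication, so that the primary outcome and the medication record agree.
3. **Role of the ICHD criteria.** The sponsor should state whether they filter the primary count, and make that choice consistent with the outcome's name and with the sample-size endpoint.
4. **The other count.** Report it as a secondary outcome where the diaries allow.

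The cost is mainly wording and re-derivation from existing diaries and medication records. Recruitment is scheduled to run until 31 December 2026 and no formal interim efficacy analysis is planned, so there is time to settle the rule without knowledge of results.

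There are two downsides. Counts will rise in both arms, by an amount the documents do not give. It must also be checked that the records capture treated headaches under 4 h, including at baseline: the article shows patients being asked about days of at least 4 h and medication use being logged during the study, but does not establish that short treated headaches were recorded from the start. If they were not, that limitation should be stated with the result.
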